##### 1. Behaviour change techniques that can be operationalised

We will develop a matrix of behaviour change techniques that can be operationalised by each IME method. This work will be done with researchers (especially health psychologists) unconnected with the project in brainstorming workshops. Project team members will present work done using paper-based and web-based IMEs, and participants will work alone to place behaviour change techniques into the matrix. Following this group discussion will be used to reach consensus on which techniques could be supported by each method. We will do this with more than one group of researchers (*e.g*., at weekly departmental research meetings at collaborator sites). Here we are looking for the method that can be to deliver most behaviour change techniques.

##### 2. Complexity of scenarios that can be delivered

We will develop a table of factors (*e.g*., people involved, context) that we are able to vary in clinical scenarios that can be delivered by each IME method. We will use brainstorming workshops involving researchers unconnected to the project to validate this list (*i.e*., do they agree with it) and make suggestions as to whether it can be extended (or reduced) for each IME method. We may use the same groups of researchers as for point one above although not at the same workshop. Here we are looking for the method that would allow more factors of a scenario to be varied.

##### 3. Identification of predictors

The first part of the web-based IME will evaluate whether the delivery mechanism of the IME (paper or web) affects predictors of GP behaviour. We anticipate that the predictors coming from the two methods will be similar because only the delivery method will be different; the web-based IME will use materials from the earlier paper-based IME. For example, evidence of habitual behaviour was strongly correlated with behavioural intention in the earlier paper-based IME. When delivering the same scenarios to GPs in a web-based IME, we anticipate (but do not know) that we will also find a strong correlation between habit and intended behaviour. Therefore, here we are seeking confirmation that delivery method alone does not lead to widely different predictors being identified by the IME.

##### 4. Recruitment (reaching target and time taken to do so)

Here, we will assess three things: time (in days) spent by the project team to recruit to target; time (in days) between sending an invitation to a potential participant and receiving a completed questionnaire; and the number of invitations necessary to receive one completed questionnaire

These will be measured in the first part of the web-based IME and compared to estimates of timing (admittedly, less accurate) from the earlier paper-based IME. We will, however, get an indication of how the two methods compare. The embedded trial of paper invitation to GPs to participate in our study versus email invitation will provide comparative data on these two recruitment methods, which will be of wider relevance than recruitment to IMEs. Here we are looking for the fastest and least labour-intense method of recruiting participants to an IME.

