#### Identifying participants

GPs will be identified by the Scottish Primary Care Research Network (SPCRN; http://www.sspc.ac.uk/spcrn/) [12] using a combination of publicly available information provided by ISD Scotland http://www.isdscotland.org/isd/3793.html[13] and restricted information held on the NHS.net database. A preliminary test of our recruitment method has identified over 3,000 GPs for whom we can obtain both email and postal addresses.

GPs receiving a postal invitation will receive a one-page letter and a two-page information sheet. Together with general information, the letter will contain a URL to the web-based IME system and a unique identifier for the GP. The identifier will be used to identify non-responders and for payment (see below). GPs receiving an email invitation will receive an email containing the same text as on the paper letter and the two-page information sheet as a pdf attachment. We will send two reminders to non-responders, the first at two weeks, the second at four weeks, using the same method as used for the initial invitation. We expect response rates of 30% to 40% based on the earlier paper-based IME [6].

Participants will be asked to complete up to two online questionnaires, which together will form a web-based IME. GPs will be paid £20 in advance in the form of a voucher for the first part of the web-based IME and £30 in advance as a voucher for the second part. A recent Cochrane review of strategies to increase response rates to postal and electronic questionnaires found that advanced payment led to a higher response rate (odds ratio = 2.00; 95% confidence interval = 1.54 to 2.60) [14]. GPs will be able to select from a list of seven types of voucher: Amazon, Argos, Boots, iTunes, Love2Shop, Marks & Spencer, or Starbucks. GPs will also be free to do the study without receiving a voucher if they so wish.

GPs will be able to decline to take part in the study by clicking a button on the second page of the web-based IME system, by emailing their ID number to a study email address, or by telephoning or sending a text message to the study mobile number. A flow diagram of the study is shown in Figure 1.

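### Secondary outcome 4 measures response speed only in GPs who complete, so a recruitment method that is never behind can still look slower

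*Protocol article*

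**What the plan says.** Under Outcome measures, item 4 (Recruitment), the protocol article lists three quantities:

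- effort: "time (in days) spent by the project team to recruit to target";
- speed: "time (in days) between sending an invitation to a potential participant and receiving a completed questionnaire";
- yield: "the number of invitations necessary to receive one completed questionnaire".

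They are measured in the first part of the web-based IME and set against estimates from the earlier paper-based IME, whose timings the article admits are less accurate. Of that comparison it says: "We will, however, get an indication of how the two methods compare". The aim is then stated: "Here we are looking for the fastest and least labour-intense method of recruiting participants to an IME". The section does not say how the three quantities are to be combined if they disagree.

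Under Identifying participants, the article states: "We expect response rates of 30% to 40% based on the earlier paper-based IME". It also states: "We will send two reminders to non-responders, the first at two weeks, the second at four weeks", by the same mode as the invitation. For the embedded email-versus-post trial, the primary outcome under Statistical analysis is the proportion completing among all GPs sent an invitation.

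**The concern.** Of the three quantities, the second is the only direct measure of how quickly GPs respond. Its definition ends at receipt of a completed questionnaire, so it has no value for a GP who never completes. Whether a GP completes is itself a result of the recruitment method. Comparing times among completers therefore compares two groups that the methods themselves selected. Reminders sharpen the problem. A GP won over by a reminder counts as a success for the method but enters the time measure as a late value. At stake is the statement about which method is fastest: it could favour the method that had recruited fewer of its invited GPs.

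**Working it through.** The article gives no computed figure for this outcome, so there is none to reproduce. The inputs from the document are the expected response rate (30% to 40%), the target of 250 completed first questionnaires, the first 500 GPs randomised (two blocks of 250), and reminders at days 14 and 28. Response is taken to mean completion.

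**1. Share without a value.** This is 1 − response rate.

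- At 40%: 0.60, or 300 of the first 500. Reaching 250 completions takes 250/0.40 = 625 invitations, leaving 375 GPs without a time.
- At 30%: 0.70, or 350 of the first 500. Reaching 250 completions takes 250/0.30 = 833.3, so 834 invitations, leaving 584 without a time.

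**2. Can the ranking mislead?** Assume completions arrive 3 days after each mailing (days 3, 17 and 31). Let two methods have the same first-wave response and totals at the two ends of the expected range. The wave shares are assumptions, as percentages of all invited.

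| | Day 3 | Day 17 | Day 31 | Total | Cumulative |
|---|---|---|---|---|---|
| Method A | 25 | 3 | 2 | 30 | 25 / 28 / 30 |
| Method B | 25 | 10 | 5 | 40 | 25 / 35 / 40 |

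Mean among completers = Σ(share × day) / Σ(share).

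- A: (0.25×3 + 0.03×17 + 0.02×31)/0.30 = 1.88/0.30 = 6.27 days.
- B: (0.25×3 + 0.10×17 + 0.05×31)/0.40 = 4.00/0.40 = 10.0 days.

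A looks 3.7 days faster, although B is level at day 3 and ahead from day 17.

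**3. The same data over all invited GPs.** Count non-completers at day 42, two weeks after the last reminder.

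- A: 1.88 + 0.70×42 = 31.3 days.
- B: 4.00 + 0.60×42 = 29.2 days.

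The order reverses. Invitations per completion agree with B: 1/0.30 = 3.33 for A, 1/0.40 = 2.50 for B.

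**4. A second pattern.** Take shares of 20/5/5 and 20/10/10 with a 5-day lag (days 5, 19 and 33). The completers' means are 3.6/0.30 = 12.0 and 6.2/0.40 = 15.5 days. Over all invited GPs to day 42 they are 3.6 + 29.4 = 33.0 and 6.2 + 25.2 = 31.4 days. The reversal is the same.

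**5. When it does not happen.** With B's completions equal to A's plus some extra ones, B's mean exceeds A's only if the extra completions arrive, on average, later than A's mean. In step 2 the extras average (0.07×17 + 0.03×31)/0.10 = 21.2 days, against A's mean of 6.27. Now take shares of 5/5/20 and 5/15/20 on days 3, 17 and 31:

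- (0.15 + 0.85 + 6.20)/0.30 = 24.0 days;
- (0.15 + 2.55 + 6.20)/0.40 = 22.25 days.

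Here the extra completions all come from a reminder, yet the mean falls, because day 17 is earlier than 24.0.

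**6. The median.** In step 2, 25 of A's 30 and 25 of B's 40 completion points fall on day 3. Both medians are 3 days, so there is no reversal, but B's higher completion does not show either.

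**The case against.** The strongest reply is that the speed measure does not stand alone. Project-team days and invitations per completed questionnaire are reported with it, and the latter counts every invited GP and would credit better reminders. The embedded email-versus-post trial is judged on completion among all GPs invited, and it has no secondary outcomes. The web-versus-paper comparison is historical and offered only as an indication. The article fixes neither mean nor median, and handling of non-completers could sit in a fuller document. Time to response among responders is also a sensible logistics description when read beside yield.

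Much of this stands, and it limits the point. A reader might infer that a method with better reminders will always be called slower. Steps 5 and 6 of the working show that this is false. A reader might also infer that the fastest method is to be chosen on completers' times alone. No sentence says so; the aim follows all three measures. Nor does the document give the paper-based IME's reminder schedule, so it cannot be said that reminders would reverse that particular comparison.

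What the reply does not remove is the definition itself. Yield and effort are not speed, and reporting them alongside leaves the speed measure uncorrected. If they point the other way, nothing says which prevails. The caution about the paper timings concerns their accuracy; more accurate dates would not remove the selection of completers.

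**Conclusion.** The point holds in a limited form. As defined, the speed measure exists only for completers, and 60% to 70% of invited GPs would have no value if the expected response rate is borne out. That rate was projected from the paper-based IME, so the actual share may differ. A completers' mean can then rank a method as slower although it has completed at least as many GPs by every day. The sizes shown, 3.7 days in one illustration and 3.5 in the other, rest on assumed wave shares and lags. They show that the error is possible, not how large it would be here. The consequence is minor: one of three components of one secondary outcome is affected, the comparison with paper is described as indicative, and neither trial's primary analysis changes.

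**What to change.** Base any statement about the fastest method on the cumulative proportion of all invited GPs who have completed by fixed days tied to the mailings, for example days 14, 28 and 42 from each GP's own invitation. Count decliners and non-responders as not completed, and read the result beside invitations per completed questionnaire. Keep completers' days as description only. If the paper-based IME's records do not give completion by day among all invited, make no claim about which is fastest against paper.

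The cost is a change of wording and one simple table. Invitation and completion dates should be readily available for the web-based study. The possible loss is the speed comparison with paper, if the older records are too coarse to support it.

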##### 5. Ability to change targeted constructs

The theories used in paper- and web-based IMEs target particular constructs (*e.g*., GPs' beliefs about antibiotic prescribing) and the effect an intervention has on these targets is measured using a score. The web-based IME will involve a direct comparison of an intervention from the paper-based IME and a new intervention that makes use of the possibilities offered by web-based delivery. We will also compare the effect on targeted constructs of the same persuasive communication intervention delivered by both methods. By comparing each IME method's ability to change scores on the targeted constructs we will be able to make a statement as to which IME method is most effective.

##### 6. Effect size for persuasive communication intervention compared to control

The persuasive communication intervention and control were delivered in an earlier paper-based IME. By delivering the same intervention in a web-based IME we can compare the effect on the primary outcome (intention to prescribe an antibiotic) of the two delivery methods. Here, we are looking for the greatest effect size.

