#### Trial procedures

Participants will be asked to complete up to two online questionnaires, which together will form a web-based IME. GPs who are already likely to be following best evidence with regard to prescribing antibiotics will be excluded from the second questionnaire, which we will do by excluding those in the first quartile of 'intention to prescribe' responses to the first questionnaire. These 25% of GPs will be thanked but will not continue in the study. Thus 75% of GPs completing the first questionnaire will be asked to complete the second. The intervention will be delivered together with the second questionnaire.

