#### Comparator

The comparator will be provision of general information about prescribing of antibiotics taken from recent reviews on antibiotic prescribing [8,9].

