### Statistical analysis

For the web-based IME trial, reporting will be in line with the CONSORT statement [25]. Data will be summarised by intervention group using appropriate descriptive statistics where required, for example, mean and standard deviation for the primary outcomes. The primary outcomes will be analysed using an analysis of covariance (ANCOVA) framework to correct for the baseline levels of intention and behavioural simulation. Effect sizes will presented with estimated 95% confidence intervals of the two new interventions versus generic information as the comparator. All analysis will be by intention to treat. Missing data at baseline are impossible by trial design, missing outcome data due to non-response to second questionnaire will not be imputed, analyses will be by responders only. Characteristics of responders and non-responders baseline data will be compared to assess the impact potential non-response on results. Secondary outcome will be analysed in a similar manner to the primary outcomes.

For the email versus postal invitation trial, reporting will also be in line with the CONSORT statement [25]. The primary outcome will be presented as the proportion of GPs sent an invitation completing the first questionnaire by invitation method. Proportions will be compared using a simple chi-square test, and results presented as an odds ratio and 95% confidence interval. There are no secondary analyses for this trial.

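### Secondary outcomes 5 and 6 set the web IME against an earlier paper IME to find a winner, but delivery mode is not randomised and no interval for the difference is stated

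*Protocol article*

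**What the plan says.** All references are to the protocol article.

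- **Outcome 5 (targeted constructs).** It includes a comparison of the same persuasive communication delivered by web and by paper, after which "we will be able to make a statement as to which IME method is most effective".
- **Outcome 6 (persuasive communication versus control).** The paper figures come from another study: "The persuasive communication intervention and control were delivered in an earlier paper-based IME". The web effect on intention is set beside them, and "Here, we are looking for the greatest effect size".
- **Trial procedures.** GPs are removed before the second questionnaire by "excluding those in the first quartile of 'intention to prescribe' responses to the first questionnaire". The result is stated as "Thus 75% of GPs completing the first questionnaire will be asked to complete the second".
- **Comparator.** For the web IME, "The comparator will be provision of general information about prescribing of antibiotics taken from recent reviews on antibiotic prescribing".
- **Statistical analysis.** "The primary outcomes will be analysed using an analysis of covariance (ANCOVA) framework", with adjustment for baseline. Effect sizes with 95% confidence intervals are planned for the two interventions against generic information. For the rest, "Secondary outcome will be analysed in a similar manner to the primary outcomes".

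**The concern.** Objective 3 asks how web and paper IMEs compare, including their effect on intended prescribing. Outcomes 5 and 6 serve that part of the objective, and each is worded to end in a winner. The two modes, however, come from two studies run at different times in different samples of GPs. Randomisation protects the comparison of the persuasive communication with control inside each study. It does not protect the comparison of one study's effect with the other's.

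No uncertainty is stated for that second comparison. The Sample size section does quantify the risk of a wrong choice between the two randomised web interventions. It offers nothing similar for web against paper, where sampling error is joined by possible differences in period, sample and entry rule. If the text is followed as written, one IME method could be called better on a difference that the design cannot attribute to the method.

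**Working it through.** **Inputs from the article (Sample size; Trial procedures):** standardised effect 0.66; 50 per group; 90% power; 5% significance; lowest quartile of intention to prescribe excluded.

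**Assumed, because the article does not give them:** paper IME size, 25 to 200 per arm; true standardised effect, 0 to 0.66; baseline to follow-up correlation r, 0.3 to 0.7; normally distributed scores.

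**1. The plan's own figure.** A two-sided t-test at d = 0.66 has power 0.899 with 49 per group and 0.904 with 50. The stated 50 per group reproduces.

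**2. Precision of web minus paper (unadjusted).** For each study, SE(d) = √(2/n + d²/(4n)).

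- Web, n = 50, d = 0.66: √(0.04 + 0.4356/200) = √0.04218 = 0.205.
- Paper also 50 per arm: SE of the difference = √2 × 0.205 = 0.290; half-width 1.96 × 0.290 = 0.57.
- Paper 25 per arm, d = 0.66: √(0.04218 + 0.08436) = 0.356; half-width 0.70.
- Paper 200 per arm, d = 0: √(0.04 + 0.01) = 0.224; half-width 0.44.

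**3. What picking the larger estimate does.** With 50 per arm in both studies, the SE of the difference is 0.28 to 0.29.

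- If the methods are truly equal, the two observed effects differ by more than 0.2 SD with probability 2Φ(−0.2/SE), about 48 to 49%.
- If they truly differ by 0.2 SD, the wrong one is picked with probability Φ(−0.2/SE), about 24 to 25%, or 19 to 29% over the assumed paper sizes.

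These figures cover chance alone and ignore confounding.

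**4. The quartile exclusion.** For a normal score cut below at its 25th percentile, a = −0.674 and λ = φ(a)/0.75 = 0.424. The variance is 1 + aλ − λ² = 0.535, a loss of 0.465. The follow-up SD becomes √(1 − 0.465r²) of its uncut value:

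- r = 0.3: 0.979, so the same raw effect looks 1/0.979 = 1.02 times larger;
- r = 0.7: 0.879, so it looks 1/0.879 = 1.14 times larger.

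This matters only if the paper IME had no comparable cut, which the article does not say.

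**5. Does the assigned analysis reach this question?** ANCOVA on the second questionnaire can estimate the persuasive communication's effect on intention and construct scores inside the web IME. Delivery mode is constant in those data, so the model cannot estimate web against paper. The article describes no pooling with individual paper data.

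**The case against.** These are two of seven secondary outcomes. The randomised primary comparison and the sample size are untouched. Objective 3 also rests on predictors, on the techniques and scenarios each method can support, on recruitment and on interviews, so an effect-size ranking would not settle it alone. An article may leave the details of a cross-study contrast to a fuller document. The intervals above are also unadjusted. With r = 0.7 within the analysed samples and baseline adjustment in both studies, the half-width at 50 per arm and d = 0 would fall from 0.554 to about 0.554 × √(1 − 0.49) = 0.40.

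Most of this stands and limits the weight of the point. It does not remove it: an interval of ±0.40 is still wide against 0.66, and the wording of outcomes 5 and 6 is stated in the article, not left to another document.

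A reader might infer several stronger things that the text does not support:

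- **That the two studies used different entry cuts.** The paper IME's entry rule is not given.
- **That the larger effect size decides which method is called most effective.** The two phrases belong to different outcomes: constructs in outcome 5, intention in outcome 6.
- **That no intervals are planned.** They are planned for the web effects against generic information and are unstated only for web minus paper.
- **That the assigned analysis cannot be run on these outcomes.** Within the web arms it can, for intention and construct scores. The workshop, recruitment and interview outcomes have their own methods described.

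**Conclusion.** The point holds for outcomes 5 and 6. Their wording promises a ranking of IME methods from a non-randomised comparison with an earlier study, and no uncertainty is stated for that contrast. The unadjusted 95% half-width is about 0.57 SD if the paper IME had 50 per arm, and 0.44 to 0.70 SD over an assumed 25 to 200 per arm, against a planned effect of 0.66. Chance, period or sample differences could each produce the ranking.

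The quartile exclusion is a secondary and conditional issue: an inflation of about 1.02 to 1.14 times on the follow-up SD, under normality with r between 0.3 and 0.7, and only if the paper IME had no such cut. A larger factor, 1/0.731 = 1.37, would arise if effects were standardised on the baseline SD, but the article does not specify that standardiser, so the figure should not be relied on.

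The effect is on part of objective 3. The randomised web comparisons remain valid.

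**What to change.** 1. In outcomes 5 and 6, remove the search for the larger effect and the statement of which method is best. Report the persuasive communication versus control effect from each study in raw scale points, and their difference with a 95% confidence interval. Label this an exploratory, non-randomised comparison with no claim of superiority.
2. Where individual data from the paper IME are held, apply the same cut on baseline intention to both studies before comparing. Otherwise state the paper IME's entry rule, and whether its control matched the web comparator, beside the result.
3. In Statistical analysis, limit the sentence on secondary outcomes so that ANCOVA applies to randomised comparisons of scores within the web IME.

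The cost is wording, one extra interval and a weaker claim for part of objective 3. Recruitment, sample size and the primary analysis do not change.
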